### 2.3. Sample Size Calculation

The total sample size was estimated through an a priori power analysis, using the G power V 3.1.9.7 software (Heinrich-Heine-Universität, Düsseldorf, Germany). The following input parameters were applied using a repeated-measure ANOVA design: effect size f = 0.33, α = 0.05, power = 0.80, and correlation between repeated measures r = 0.50. The a priori power calculation revealed that the initial sample size required is 11. By considering a 10% dropout rate, 13 individuals with Parkinson’s disease will be recruited to voluntarily participate in this study.

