### 2.7. Outcome Measures

Volunteers will attend both conditions (synchronous and asynchronous remote video-based) in a randomized order, separated by a washing-out period of at least a week. Kinematic, DLPFC hemodynamic activity and levels of anxiety data will be collected before (base-line data) and after the two interventions, while, on a third occasion, control data will be collected at the same time points but without any intervention.

Two experienced evaluators blinded to the group allocation will collect data. Baseline data collection will include: (1) Anthropometric characteristics (sex, age, body mass index), H&Y scale; (2) Anxiety Hamilton Rating Scale (Hamilton 1960); (3) Gait analysis using a 10-camera 3D motion analysis system (Vicon T-series, Oxford, UK) and two force platforms (Bertec 4060–10, OH) embedded in the laboratory floor; (4) Frontal cortex hemodynamic responses using f-NIRS (Portalite by Artinis NL); and (5) Unified Parkinson’s Disease Assessment Scale-III (UPDRS-III). Post intervention measurements will include: (1) Anxiety Hamilton Rating Scale (Hamilton 1960); (2) Gait analysis using a 10-camera 3D motion analysis system (Vicon T-series, Oxford, UK) and two force platforms (Bertec 4060–10, OH) embedded in the laboratory floor; (3) Frontal cortex hemodynamic responses using f-NIRS (Portalite by Artinis NL); and (4) Unified Parkinson’s Disease Assessment Scale-III (UPDRS-III).

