### 2.10. Statistical Analyses

The normal distribution of the dataset will be assessed using the Shapiro–Wilk test. Analyses of variance (ANOVAs) with repeated measures will be used to analyze kinematic and kinetic parameters and pre-frontal cortex hemodynamic responses during gait initiation and during the steady state between the two interventions and time points. Significant interactions and main effects will be further examined using Bonferroni post hoc analysis. The significance level will be set at *p* < 0.05.

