Given that recent research on rhythmic training has yielded beneficial results using methods such as rhythmic auditory stimulation (RAS) or dance, which includes rhythm as a key component, it is expected that the said MSK program will be an effective non-pharmacological intervention in dealing with PD-derived gait impairments. Finally, it is expected that both means, synchronous on site and tele format, will be equally effective in regulating the aforementioned biopsychological parameters as the content of the class and teaching styles will be the same. Research on the use of remote dance programs for people with PD has indicated acceptable feasibility and significant improvements in depression and quality of life, but at the same time has underlined the importance of live dance [27,28].

In general, patients with PD frequently experience disruptions in the 24 h daily profile of both behavioral and biological markers [29]. This lack of rhythmicity or disruption of inner-rhythm can negatively affect elements of health [30,31] and physical performance [32]. Therefore, it is rather prudent to establish non-pharmacological strategies able to reduce the global impact of the disease and improve the quality of life of both patients and the patient’s caregiver.

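### Plain Bonferroni after a significant ANOVA effect is valid but needlessly conservative; Holm's method keeps the same error rate for a modest gain in power

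*Protocol article*

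**What the plan says.** Section 2.10 plans repeated-measures ANOVAs of the gait and hemodynamic outcomes "during gait initiation and during the steady state between the two interventions and time points". It continues: "Significant interactions and main effects will be further examined using Bonferroni post hoc analysis". The level is fixed in the same place: "The significance level will be set at *p* < 0.05".

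A follow-up comparison therefore has to pass two hurdles: a significant F, and then a Bonferroni-adjusted test. The section does not say which comparisons make up the Bonferroni family.

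Three other places bear on the point:
- Section 2.7 adds a control session: "on a third occasion, control data will be collected at the same time points but without any intervention".
- Section 2.3 plans with "effect size f = 0.33, α = 0.05, power = 0.80, and correlation between repeated measures r = 0.50" and reports: "The a priori power calculation revealed that the initial sample size required is 11". Then: "By considering a 10% dropout rate, 13 individuals with Parkinson’s disease will be recruited".
- Section 3 expects no difference between the formats: "it is expected that both means, synchronous on site and tele format, will be equally effective".

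**The concern.** The post hoc step is where the trial would say which format changed and whether the formats differ after class. With 11 to 13 people, power is scarce there. Plain Bonferroni gives some of it away without buying any error control in return, because Holm's method has the same guarantee under the same conditions.

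How much is given away depends on the family. In a layout of two interventions by two time points each main effect has two levels, so Bonferroni has nothing to adjust there. It acts only on comparisons made after a significant interaction. If those are all pairs of cells, the divisor is 6, or 15 with the control session, and it includes pairs that estimate no treatment effect.

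**Working it through.** **Inputs from the article.** Level 0.05, f = 0.33, r = 0.50, power 0.80, N = 11 before and 13 after dropout; two interventions by two time points in section 2.10; a third, control session in section 2.7.

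**Assumptions not in the article.** Normal data, unit SD, equal correlations of 0.50, two-sided paired t-tests, and the effect sizes below. With r = 0.50 the SD of a pre-post change is √(2 × (1 − 0.50)) = 1, so a change of 1.2 SD is also a standardised paired effect of 1.2.

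**1. The plan's own figure.** For a within-subject F with m measurements, λ = f² × N × m / (1 − r). With one group and m = 6, λ = 0.1089 × 11 × 6 / 0.50 = 14.4 on 5 and 50 degrees of freedom. Power is 0.802, so N = 11 is reproduced. One group with m = 4 would need 14. Dropout: 11 / 0.90 = 12.2, rounded up to 13. The sample size thus covers an F test at 0.05; no adjusted comparison is powered.

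**2. Counting pairs, if the family is all cell pairs.**

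| Layout | All pairs | Pre-post, same session | Post-post | Pre-pre | Both session and time differ |
|---|---|---|---|---|---|
| 2 × 2 | 6 | 2 | 1 | 1 | 2 |
| 3 × 2 (with control) | 15 | 3 | 3 | 3 | 6 |

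The pre-post and post-post pairs bear on the aims: 3 of 6, or 6 of 15.

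**3. Cost of the divisor.** A paired comparison with 80% power at 0.05 (n = 13, standardised effect 0.847) has about 62% at 0.05/3, 49% at 0.05/6 and 34% at 0.05/15.

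**4. Two-by-two layout, n = 13, simulated.** The endpoint is that both the better format's pre-post change and the post-post difference are significant, given a significant interaction. Figures agree between runs to about one point.

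| True changes (SD) | Interaction significant | Bonferroni, 6 pairs | Holm, 6 pairs | Holm, 3 relevant pairs |
|---|---|---|---|---|
| 0.9 and 0 | 56% | 59% | 66% | 83% |
| 1.2 and 0 | 80% | 86% | 90% | 97% |
| 1.2 and 0.4 | 47% | 66% | 74% | 86% |

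Multiplying by the chance of a significant interaction gives the unconditional figures, Bonferroni to Holm: 33% to 37%, 69% to 72%, and 31% to 35%. For example, 0.56 × 0.59 = 0.33 and 0.56 × 0.66 = 0.37. If the two formats are equally effective, the interaction is significant about 5% of the time and the gain is 0.2 to 0.3 points.

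**5. Three sessions.** The comparisons are the three pairwise differences in pre-post change; both formats change by 1.2 SD and control by 0. The chance of showing both formats against control at n = 13 is 45% with Bonferroni, 53% with Holm, and 68% with the closed test (each pair at 0.05 after a significant overall F, valid for exactly three sessions). At n = 11 these are about 33%, 41% and 57%. Under the complete null the F gate plus Bonferroni has a simulated familywise error of 0.032, against 0.050 for the closed test.

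**The case against.** The strongest reply is that nothing here is wrong. Bonferroni is valid, and a condensed article may leave the exact family to a fuller document. That stands: this is inefficiency in a stated rule, not bias or contradiction.

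Three stronger readings are tempting, and none is supported.

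- **The plan tests every cell pair, at least half of them useless.** Section 2.10 names no family, so all pairs is an inference. If the follow-up is one pre-post test per format, there is no Bonferroni penalty. The share of uninformative pairs also depends on counting pre-pre pairs, which can bear on carry-over in a crossover. Without them it is 2 of 6 (33%) or 6 of 15 (40%).
- **Holm would rescue a significant interaction left with no supporting comparison.** It cannot on the same family, because its first step is the Bonferroni test of the smallest p value. In the three scenarios no pair was significant in 6.9%, 0.9% and 1.0% of runs with a significant interaction, identically for both methods. Only a shorter family could help.
- **The loss is large in the trial as planned.** The 4-to-9-point gains require a significant interaction and two comparisons succeeding together. They also assume unequal formats, whereas section 3 expects equal ones. The three-session figures apply only if control enters the analysis, which section 2.10 does not describe.

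**Conclusion.** The point holds as a modest efficiency improvement. On any family of two or more comparisons Holm is never worse than Bonferroni and has the same error guarantee; that part needs no assumption about effects.

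The size does need assumptions. At n = 13 and r = 0.50 the gain is about 4 to 9 points given a significant two-by-two interaction, about 4 points unconditionally, near zero if the formats are equally effective, and 8 points (45% to 53%) for both formats against control over three sessions. If the family is all cell pairs, shortening it matters more than the swap: in the two-by-two scenarios Holm on the 3 relevant pairs reaches 83%, 97% and 86%, against 66%, 90% and 74% for Holm on all 6.

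**What to change.** In section 2.10, replace the Bonferroni wording with: *Holm-adjusted comparisons, limited after a significant interaction to the pre-post change within each session and the post-vs-post difference between sessions.* This gives 3 comparisons in the two-by-two layout and 6 if control is included.

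Two riders are needed:
- In the two-intervention layout, the between-format difference in pre-post change is the interaction F test itself (t² = F). It is tested once at 0.05 and must not be adjusted again. Placing it in a Holm family of three would cut its power from 56% to 41%, 80% to 68% and 47% to 35% in the three scenarios.
- If the control session is included, the three pairwise differences in change may each be tested at 0.05 after a significant overall F (closed test).

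The change needs no extra data or participants. Its one downside is that Holm gives no simple simultaneous confidence intervals, so unadjusted 95% intervals would be shown beside the adjusted p values and labelled as such.

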## 3. Expected Results

The aim of the proposed study is to examine the acute effects of a MSK program on anxiety levels and select kinematic and kinetic parameters alongside DLPFC hemodynamics during gait initiation and steady-state walking in individuals with PD, performed in the following conditions: (a) synchronous learning format and (b) asynchronous remote video-based format. The program is customized for PD patients without deviating from the objectives of musicokinetic education. Primary outcomes will be the acute effects of a MSK protocol in people with PD on anxiety and locomotion. Secondary outcomes will be the effectiveness of asynchronous remote video-based format for those patients that are not able to attend classes on site. To our knowledge, this is the first time that MSK program will be introduced in PD as a form of exercise. Since motor dysfunctions are associated with anxiety [2], rhythmic-based interventions can potentially improve or even regulate it.

Anxiety may be a result of the neurochemical changes of the disease itself or a psychological reaction to the stress of the disease, and can be seen in various manifestations such as phobia, generalized anxiety disorder, or panic attacks [3,26]. The rationale behind the use of the purpose-designed MSK program for PD is its effectiveness in addressing the primordial motor expression of humans. Guidance by the rules of music, where periodicity is distinct, may eventually be beneficial in “calibrating” the brain, reducing motor difficulties, restoring movement harmony, and, thus, reducing anxiety. Moreover, we expect that the combined influence of improved rhythmicity, potentially improving the automatization of motor control, would be reflected in decreased DLPFC activation due to reduced executive load in the planned control of movements.

Given that recent research on rhythmic training has yielded beneficial results using methods such as rhythmic auditory stimulation (RAS) or dance, which includes rhythm as a key component, it is expected that the said MSK program will be an effective non-pharmacological intervention in dealing with PD-derived gait impairments. Finally, it is expected that both means, synchronous on site and tele format, will be equally effective in regulating the aforementioned biopsychological parameters as the content of the class and teaching styles will be the same. Research on the use of remote dance programs for people with PD has indicated acceptable feasibility and significant improvements in depression and quality of life, but at the same time has underlined the importance of live dance [27,28].

In general, patients with PD frequently experience disruptions in the 24 h daily profile of both behavioral and biological markers [29]. This lack of rhythmicity or disruption of inner-rhythm can negatively affect elements of health [30,31] and physical performance [32]. Therefore, it is rather prudent to establish non-pharmacological strategies able to reduce the global impact of the disease and improve the quality of life of both patients and the patient’s caregiver.

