### 2.9. Secondary Outcome Measures

Demographic and anthropometric measurements: age, sex, body mass index, marital status, educational level, profession, duration of the disease, medication and symptomatology. According to the WHO protocol (2016), body mass index (BMI) is classified as follows: thin (BMI < 18.5); eutrophic (BMI 18.5–24.9); overweight (BMI 25.0–29.9); pre-obesity and obesity (BMI > 30.0).

Unified Parkinson’s Disease Assessment Scale-III (UPDRS-III): The maximum value indicates greater involvement of the disease and the minimum normality. The UPDRS-III is a reliable (r-0.96) and valid scale.

The effectiveness of the synchronous learning format vs. the asynchronous remote video-based format will be based on the results of the aforementioned measurements and the response of patients who complete the protocol.

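### The stated difference test, in 11 to 13 people, cannot establish the expected equal effectiveness of the live and video formats

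*Protocol article*

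**What the plan says.** All references are to the protocol article.

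- **Expectation.** Section 3 states that "it is expected that both means, synchronous on site and tele format, will be equally effective", and applies this to all the parameters under study. The reason given is that class content and teaching style are the same. No tolerated difference is attached.
- **Status of the comparison.** Section 2.9 lists it among the secondary outcomes: "The effectiveness of the synchronous learning format vs. the asynchronous remote video-based format will be based on the results of the aforementioned measurements". The sentence then adds a second basis, the response of patients who complete the protocol. The Introduction and section 3 describe the secondary outcome as how effective the video format is for patients who cannot come to the site.
- **Analysis.** Section 2.10 plans repeated-measures ANOVA of outcomes "during gait initiation and during the steady state between the two interventions and time points". It continues: "Significant interactions and main effects will be further examined using Bonferroni post hoc analysis". And: "The significance level will be set at *p* < 0.05".
- **Sample size.** Section 2.3 uses "effect size f = 0.33, α = 0.05, power = 0.80, and correlation between repeated measures r = 0.50" and concludes that "the initial sample size required is 11", raised to 13 for 10% dropout.

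**The concern.** The expectation is one of equality, whereas both the test and the sample size are built to find a difference. A difference test can contradict an expectation of equality. It cannot confirm one, because a non-significant result is what one sees both when the formats are alike and when the trial is too imprecise to tell them apart. The smaller or noisier the trial, the more often that result occurs.

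The stake is the advice given to patients who cannot travel, for whom the video format is intended. If it is less effective than the live class by a moderate amount, this trial would probably not detect that, and its result could look as though it agreed with section 3. Section 3 itself notes that earlier remote-dance research stressed the importance of live dance, so a real difference is not far-fetched.

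**Working it through.** **1. The plan's own figure.** Section 2.3 gives f = 0.33, α = 0.05, power 0.80 and r = 0.50, but not the number of measurements. For a within-subject ANOVA factor with m measurements and one group, taking sphericity as met:

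- λ = f²·N·m/(1 − r), with df m − 1 and (N − 1)(m − 1).
- Assumption: m = 6, from three occasions (live, video, control) with two time points each.
- N = 11: λ = 0.1089 × 11 × 6 / 0.5 = 14.37, df 5 and 50, power 0.802. N = 10 gives 0.751.
- With m = 2, 3 or 4, N would be 21, 17 or 14.
- Dropout: 11/0.9 = 12.2, rounded up to 13.

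So 11 and 13 reproduce. That power, however, belongs to a 5-df omnibus test of difference among six measurements, not to the live-versus-video contrast.

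**2. Precision of the format contrast.** The quantity of interest is the change under the live format minus the change under video, within person. If all four measurements have common SD and common correlation r, its SD is √(4(1 − r)) in units of the outcome SD. The 95% half-width is t(0.975, n − 1) × SD/√n.

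| r | SD of contrast | n | t | 95% half-width (SD) |
|---|---|---|---|---|
| 0.50 | √2 = 1.414 | 13 | 2.179 | 0.85 |
| 0.50 | 1.414 | 11 | 2.228 | 0.95 |
| 0.80 (assumed) | √0.8 = 0.894 | 13 | 2.179 | 0.54 |
| 0.80 (assumed) | 0.894 | 11 | 2.228 | 0.60 |

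**3. How often a real deficit would be non-significant.** Two-sided paired t test at 5%, with noncentrality (true deficit / SD of contrast) × √n. For a 0.5 SD deficit, r = 0.50 and n = 13 this is 0.354 × √13 = 1.27.

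| True deficit of video | r = 0.50, n = 13 / 11 | r = 0.80, n = 13 / 11 |
|---|---|---|
| 0.5 SD | 78% / 81% | 54% / 61% |
| 0.7 SD | 62% / 68% | 26% / 35% |

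The 0.5 and 0.7 SD deficits are illustrations. The article names no difference between formats that would matter.

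**4. What an equivalence test could do with this sample.** No margin is given, so a range is assumed, here in units of the SD of the within-person contrast. Two one-sided tests at 5% each, true difference zero (simulated):

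| Margin | Power, n = 11 / 13 | N for 80% power |
|---|---|---|
| 0.3 | 0.2% / 0.2% | 97 |
| 0.5 | 8.5% / 13.5% | 36 |
| 0.8 | 59% / 72% | 15 |
| 1.0 | 85% / 92% | 11 |

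Multiplying by the SD of the contrast gives outcome units. A margin of 1.0 is 1.41 outcome SD at r = 0.50 and 0.89 at r = 0.80.

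**The case against.** The strongest reply is that the article contains no faulty decision rule.

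- **No rule equating non-significance with equivalence.** A reader might infer from the expectation and the test together that a non-significant ANOVA will be declared equivalence, or that a worse video format would be endorsed. No section says so, and no endorsement criterion exists. This stands, and the point does not depend on that inference.
- **No equivalence objective.** The secondary outcome is worded as effectiveness of the video format and as a comparison, not as equivalence or non-inferiority. For patients who cannot attend, video against no intervention is also a relevant question, and the design has a control occasion. This stands too.
- **An expectation, not a hypothesis.** The sentence sits under expected results, comes with a reason, and is tempered by the sentence after it. Expecting no difference and testing for one is legitimate, since a significant result would refute the expectation. That is true, but the opposite result would not support it.
- **Another basis for judgement.** Section 2.9 also names patients' response, so the ANOVA is not the only evidence foreseen. It is the only analysis stated, and the article does not say how response would be judged.
- **The size depends on r.** This stands. The protocol's 0.50 is applied here to every pair of measurements, and a higher correlation reduces the problem considerably.
- **A margin may be in an analysis plan not shown.** Its absence from the article is not the complaint. The mismatch lies in what the article does fix: an expectation of equality, a difference test, and a sample sized for a difference.

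It is also tempting to compare the interval with one effect the trial is sized on. The article gives only f = 0.33, which corresponds to different gaps between means depending on their pattern, so that comparison is not made here.

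**Conclusion.** The point holds in limited form. No result of the stated test can establish that the two formats are equally effective, and with 11 to 13 completers a non-significant format effect is more likely than not even if video is worse by 0.5 SD: 78% to 81% of trials at r = 0.50, and 54% to 61% at r = 0.80. Differences of 0.85 to 0.95 SD either side of the estimate, or 0.54 to 0.60 SD at the higher correlation, would remain within the 95% interval.

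These figures assume equal SDs, one common correlation across all sessions, and a paired t analysis of the change scores. A 0.7 SD deficit would usually be missed at r = 0.50 (62% to 68%) but not at r = 0.80 (26% to 35%). The logical point does not depend on r. The sample-size arithmetic is not at fault: it reproduces with six measurements, but it answers a different question.

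**What to change.** In section 2.10:

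1. Report the live-minus-video difference in change for each outcome with its 95% confidence interval.
2. State that a non-significant format effect will not be read as equal effectiveness.
3. Claim equivalence only if the 90% confidence interval lies wholly inside a margin that is justified and fixed before the data are analysed. Otherwise state which differences the interval does not exclude.

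The cost is a few sentences, with no extra patients, visits or measurements. The downside is that with 11 to 13 people an equivalence claim will probably not be reached unless the margin is wide. Even with an observed difference of exactly zero, the 90% half-width at r = 0.50 is about 1.782 × 1.414/√13 = 0.70 SD with 13 completers and 1.812 × 1.414/√11 = 0.77 SD with 11. The sponsor may therefore have to give up the conclusion that the formats are equally effective, or enlarge the trial to suit a chosen margin.
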